## Design

INSIGHTS-GHT is a post-marketing, multicentre, prospective, non-controlled, non-interventional registry. It allows for structured, non-interventional collection of data.

### Observational plan

Participating physicians will not be subject to any instructions regarding the diagnosis and therapy of their patients. All examinations performed depend on the discretion and clinical routine of the physician.

The registry contains a basic set of variables (mandatory data) which are essential for all included patients. Another set of variables (facultative data) can be requested from the participating sites but is left to their discretion. The platform is designed to accommodate substudies (i.e., addition of further variables) in selected centres to facilitate research collaboration between institutions.

### Setting

This registry will be performed in approximately 60 specialized endocrinology sites in Germany that have expertise in growth hormone therapy. Any decision to prescribe these products will be made at the discretion of the treating physician and independent from and before any participation in this registry.

### Characteristics of patients

The eligible registry population will consist of children and adults of any age and of all sexes (male, female, diverse).

There is no formal screening procedure for suitable patients. Physicians are requested to assess all patients receiving somatropin products (already treated or newly to be initiated) for potential suitability for inclusion in the registry.

Patients are eligible for documentation if they.Are treated with any approved somatropin product,Are treated within the labelling of the respective product,Are available for long term follow-up documentation,(Or their parents/guardians, respectively) have provided informed consent.

Patients may change the somatropin product at any time, also repeatedly, during the course of documentation.

Patients are not eligible if they concurrently participate in a GH-related controlled clinical trial.

## Processes

### Treatment

Any approved somatropin product may be documented during the registry if used within its respective labelling at the time of documentation. In the protocol, the product names or manufacturers are not specified as during the course of the registry the availability of products or their labelling may change.

Detailed conditions for the use of the somatropin products and contraindications, special warnings and precautions for use are described in accordance with the marketing authorization in the Summary of Product Characteristics (SmPC) and/or the prescribing information.

### Interruption or discontinuation of GHT

Once included in the registry, it is anticipated that children will be treated with somatropin until achieving final height.

However, somatropin treatment may be interrupted or prematurely discontinued. Patients who interrupt GHT for any reason may remain in the registry to be further documented, or if they resume GHT at a later stage, continue documentation under the original patient number.

Every patient has the right to withdraw his/her Informed Consent for the surveillance at any time without giving any reason. All data generated up to the time of withdrawal of the Informed Consent or discontinuation from the surveillance including all periods of interruption of somatropin treatment will be analysed and the reason(s) for each interruption and the definite discontinuation will be recorded.

### Concomitant medication

All concomitant medications will be documented with generic drug name (INN) or trade name, with start and stop dates.

### Visit schedule and assessments

The frequency of visits is at the discretion of the treating physician. It is expected that for each patient 1 to 2 visits per year are documented. At each visit, relevant information since the last documentation is collected.

Documentation of data from visits can be performed onsite or remotely (e.g., via telephone or video chat), however such data must be part of the patient charts (exception: data from PRO questionnaires). For the documentation, the following forms are available: inclusion visit, follow-up visit, former medication, current medication, other (non-GH) medication, adverse events.

Owing to the observational study type, no additional or specific visits, tests or assessments are required for the purposes of this registry (exception: PRO questionnaires).

### Inclusion Visit

At the Inclusion visit, the following data will be recorded, if available.^1^Date of Informed Consent (mandatory)Date of visit/ contact with patientDemographics: year of birth, month of birth*, sex, ethnicityPhysical examination: height, sitting height, weight, systolic and diastolic blood pressure, heart rate, head circumferencePrevious participation in other GH databases (registries, non-interventional studies (NIS), other): NIS/registry name, if available patient IDPrevious or current participation in a clinical trial (which does not investigate GH products): start/stop date, indication

Indication for GHT: date of diagnosis, diagnosis.

*Parents’ height, height and weight at start of GH therapy.

*Birth history: Gestational age, birth weight and length, head circumference.

*Pubertal development: Tanner stages (pubic hair, breast development, male genitals); testicular volume in males, start date of puberty, spontaneous/induced puberty, menarche in females.

*Bone age: method, dates and results of current and previous (before start of GHT) evaluations.

Bone density: method, dates and results of current and previous (before start of GHT) evaluations.

Body composition: method (DXA or impedance) and device for measurement; dates and results for fat mass, lean body mass, total body water.

Prior and concomitant diseases (including information on scoliosis).

Patient-related outcomes: Short Form 12 (in adults and adolescents aged 14 years and over).

Former GHT: product name, start/stop date, reason for discontinuation.

Current GHT: product name, formulation and strength, body weight at first dose, start/stop date.

Concomitant medication: generic name or trade name, start/stop dates.

Laboratory results before start of GHT (value, date and assessment, if not otherwise specified).

Glucose metabolism: HbA_1C_Lipid status: LDL cholesterol, HDL cholesterolHormone analysis (date, assessment and substitution): thyroid axis, gonadal axis, adrenal axis, pituitary axisResults of GH stimulation tests: Arginine Infusion Test,*Clonidine Test (paediatric only), Insulin Hypoglycaemia Test (IHT), GHRH-Arginine Test, other testsIGF-I and IGFBP-3 (value, date, assessment, SDS, normal range, assay)

Laboratory values: value, date and assessment

IGF-I and IGFBP-3 (value, date, assessment, SDS, normal range, assay)Glucose metabolism: glucose, insulin, HbA_1C_Inflammation parameter: C-reactive proteinLipid status: LDL cholesterol, HDL cholesterol

Function of other pituitary axes (thyroid-, gonadal- and adrenal axis, AVP deficiency): sufficient/insufficient, adequately replaced if insufficient?

Genetics, morphology, additional pituitary hormone deficiencies.

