## Methods

### Objectives and endpoints

The objectives and corresponding endpoints of the registry are shown in Table 1.

**Table 1 Tab1:** Objectives and endpoints

	**Objective**	**Endpoints**
**Primary**	To analyse somatropin drug utilization within routine clinical practice in a diverse population of children and adults, across all GH products To determine the place of long-acting GH in practice	Utilized GH preparations Dose and dosing schedule (daily vs. long-acting) Duration of treatment Persistence Switches between GH treatments Interruption/ discontinuation of GH treatment
**Secondary**	**Efficacy** To describe the long-term efficacy of somatropin To assess the transition from adolescence to adulthood	Paediatric indications: Real final adult height (using stadiometer) Adult indication: Body composition (all methods) Delta IGF-I standard deviation score (SDS, change during treatment / normalization) Delta height standard deviation score (SDS) / delta lean body mass Body proportions (sitting height; standing height), Delta target height vs height SDS Lipid status, inflammation markers, IGF-I, blood pressure Analyses stratified according to different diagnosis groups
	Persistence	Persistence calculated as duration of time from initiation to discontinuation of therapy
	Patient related outcomes (PRO) To describe patient PRO, including quality of life and patient experience over the initial 2 years of GH treatment, cross-sectional and long term (children and adults)	Satisfaction with treatment experience Quality of life, e.g., by SF-12 (in adults and adolescents) Additional validated self-reported or observed (e.g., parent- or partner-rated) QoL and PRO questionnaires can optionally be used
	**Safety** To describe the long-term safety of somatropin	Number and rate per patient-years of Adverse events All causally related and/or temporally associated AEs
**Exploratory**	Exploratory: To assess / analyse additional parameters potentially modulated by GHT To assess subgroups of the population under observation, or to assess outcomes by participating centres	e.g., body composition by DXA

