### Descriptive analysis and statistical testing

Data will be analysed in regular (e.g., six months) intervals. This will be done to keep sites appraised of the progress of the registry and to review data quality (rate of missing values; data distribution, outliers).

All background variables and outcome parameters will be analysed descriptively with appropriate statistical methods: categorical variables by frequency tables (absolute and relative frequencies) and continuous variables by summary statistics (i.e., mean, standard deviation, minimum, median, quartiles and maximum). Continuous variables will also be described by absolute value and as change from baseline per analysis time point, if applicable.

Analyses will be performed for the total study population (overall analysis) and separately by indication or relevant subgroups (e.g., age, sex, GH pretreated and treatment-naive patients), if patient numbers are sufficient. Pretreated patients are here defined as patients already on treatment when enrolled in the study, whereas treatment-naive patients will be patients newly starting GHT.

The Statistical Analysis Plan (SAP) will specify details of the analysis.

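### No pre-treatment body composition value is requested for patients enrolled on GH, although body composition is the adult efficacy endpoint and delta lean body mass is a named endpoint

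*Protocol article*

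**What the plan says.** **Who enrols.** Under Characteristics of patients: "Physicians are requested to assess all patients receiving somatropin products (already treated or newly to be initiated) for potential suitability". Under Descriptive analysis and statistical testing: "Pretreated patients are here defined as patients already on treatment when enrolled in the study".

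**What is to be estimated.** Table 1 (Objectives and endpoints) gives as a secondary efficacy endpoint "Adult indication: Body composition (all methods" and lists "Delta height standard deviation score (SDS) / delta lean body mass". It also lists "Lipid status, inflammation markers, IGF-I, blood pressure", without wording these as changes.

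**What is collected at inclusion.** The Inclusion Visit section asks for "Bone density: method, dates and results of current and previous (before start of GHT) evaluations". Bone age is worded the same way. A separate laboratory block covers the time before GHT and includes HbA1c, LDL, HDL, IGF-I and IGFBP-3. A starred item asks for height and weight at the start of therapy. The line directly after bone density reads "Body composition: method (DXA or impedance) and device for measurement; dates and results for fat mass, lean body mass, total body water".

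**How it is analysed.** "Continuous variables will also be described by absolute value and as change from baseline per analysis time point, if applicable". The analysis is planned for the total population, and separately for subgroups including pretreated and treatment-naive patients if numbers suffice. Baseline is not defined there.

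**The concern.** A delta reads as response to treatment only if its starting value precedes treatment. In a patient newly starting GHT, the inclusion value can serve. In a patient enrolled on GHT, the value has to be retrieved from the chart, and the inclusion list does this for several items but not for body composition.

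What is at stake is what the registry can conclude about adult response. In pretreated patients, change in lean body mass would describe maintenance since enrolment. The analysis plan cannot repair this, because it cannot recover a value that was never collected.

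**Working it through.** No published figure can be reproduced here. The check sets the Table 1 endpoints against the inclusion items.

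| Item | Role in Table 1 | Pre-GHT value requested at inclusion? |
|---|---|---|
| Body composition, lean body mass | Adult efficacy endpoint; delta lean body mass named | No |
| Height | Delta height SDS named | Yes, height at start of therapy (starred item) |
| IGF-I | Delta IGF-I SDS named | Yes |
| LDL, HDL | Listed as lipid status, no delta | Yes |
| C-reactive protein | Listed as inflammation markers, no delta | No, current laboratory block only |
| Blood pressure | Listed, no delta | No, inclusion examination only |
| Bone density | Not listed | Yes |
| Bone age | Not listed | Yes |
| HbA1c | Not listed | Yes |

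1. Table 1 words three endpoints as a change in the patient: IGF-I SDS, height SDS and lean body mass. (Its comparison of target height with height SDS is a difference between two heights, not a change from a starting value.) Two of the three have a requested pre-treatment value; lean body mass does not.

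2. Bone density has no place in Table 1 and does get a pre-treatment value. The collection list and the endpoint list are therefore not aligned.

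3. For a pretreated patient, the earliest body composition value that the list asks for is the one at inclusion, which is on treatment.

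4. Effect on a pooled delta. Let p be the share of pretreated patients among those with a delta, R the mean change from start of GHT in naive patients, and M the mean change since enrolment in pretreated patients. If inclusion values serve as baseline throughout:

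   pooled mean delta = (1 − p) × R + p × M

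   This equals R only if p = 0 or M = R. The article gives no value for p, R or M, so the departure from R has no computable size. If M is taken as exactly 0, the pooled mean is (1 − p) × R, but that is an assumption.

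**The case against.** **The plural may already allow older results.** The inclusion line says dates where the follow-up line says date, and bone age and bone density show the same shift. Because GHT start dates are recorded, an older dated result could be classed as pre-treatment afterwards. This is possible, but the line neither requests nor labels such a result, and the neighbouring line does so explicitly. The full protocol or eCRF may hold the field; if so, confirming it settles the point.

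**Naive and pretreated patients are to be analysed separately.** This stands as a real mitigation, since it separates response from maintenance. It depends on sufficient numbers, an overall analysis is planned as well, and it gives pretreated patients no starting value.

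**Baseline definition belongs in the analysis plan.** Agreed, and its absence from the article is no fault. The point here is which values are collected.

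**Everything is recorded only if available, and no extra tests are required.** True. Some patients never had a pre-treatment measurement, and rewording will not create one. The same limit applies to bone density and the pre-treatment laboratory values, which are nevertheless requested.

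**Stronger readings that the article does not support.**
- A reader might infer that blood pressure and C-reactive protein have the same defect. Table 1 does not word them as changes; they become change variables only through the general rule, which applies where applicable.
- A reader might infer that the adult endpoint is biased towards no effect, or that deltas in one table will rest on different baselines. No section fixes which baseline is used, so both are conditional.
- A reader might put numbers on the dilution, for example 70%, 50% or 20% of the true change with 30%, 50% or 80% pretreated. Those follow only from assumed shares and an assumed delta of zero in pretreated patients.

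**Conclusion.** The point holds for body composition, and for delta lean body mass in particular. As the article lists the items, patients enrolled on treatment have no requested pre-treatment value for the named adult efficacy endpoint, although such values are requested for items of less weight in Table 1. A delta in the overall analysis would mix two quantities if inclusion is used as baseline.

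Treatment-naive patients are unaffected, provided their inclusion value is taken at or before the start of GHT. The endpoint is secondary and the registry mainly descriptive, so this is an inexpensive improvement to data capture and does not invalidate the design. The conclusion rests on the printed item list being complete on this line.

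**What to change.** - Give the body composition line at inclusion the same current-plus-pre-treatment wording as the bone density line, keeping method and device for each measurement. Values come from the chart where available; no new tests are needed.
- Compute delta lean body mass from the pre-treatment value where one exists. Report patients without one separately, labelled as change since enrolment.
- Optionally, add pre-treatment blood pressure and C-reactive protein. These are secondary.

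**Cost.** A few optional retrospective fields and chart look-up. The Conclusion reports 770 patients enrolled by 8 May 2023 with 23 centres contributing, against an aim of at least 1500 in the Discussion. Those of the 770 who enrolled on treatment would need back-filling. Retrieved measurements may come from a different method or device, which is why both must be recorded. The number of patients with a true delta will be smaller than the number documented and should be reported alongside it.

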### Follow-up documentations

During the follow-up periods, information will be collected during visits of the patient or via telephone or video contacts at intervals corresponding to routine clinical practice (usually once or twice yearly).

Physical examination: height, sitting height, weight, systolic and diastolic blood pressure, heart rate, *head circumference.

Current participation in a clinical trial: start/stop date, indication.

*Pubertal development: Tanner stages (pubic hair, breast development, male genitals); testicular volume in males, start date of puberty,,spontaneous/induced puberty, menarche in females.

*Bone age: method, date and result.

Bone density: method, date and result.

Body composition: method (DXA or impedance) and device for measurement; date and results for fat mass, lean body mass, total body water.

New and resolved concomitant diseases: with start/stop date.

Patient-related outcomes: i.e., SF-12 in adults and adolescents aged 14 years and over.

Current GHT: product name, formulation and strength, body weight at first dose, start/stop date, if applicable, reason for discontinuation.

Concomitant medication: generic or trade name, start/stop dates.

Laboratory values: value, date and assessment.

IGF-I and IGFBP-3 (value, date, assessment, SDS, normal range, assay).

Glucose metabolism: glucose, insulin, HbA_1C_.

Inflammation parameter: C-reactive protein. 

Lipid status: LDL cholesterol, HDL cholesterol.

Function of other pituitary axes (thyroid-, gonadal- and adrenal axis, AVP deficiency): sufficient/insufficient, adequately replaced if insufficient?

Quality of life (QoL) will be assessed with a validated generic QoL instrument (SF-12). Other instruments/ questionnaires may be added during the course of the registry or be used for specific cross-sectional evaluations.

### Subject completion

Subject may be followed up in the registry until the final registry termination. There is a planned minimum follow-up period of 3 years, but no maximum follow-up period. Interruptions of GHT are acceptable, and in such cases the patient can remain in the registry. Switches from one to another GH preparation does not qualify as subject completion, i.e., patients can remain in the registry.

### Subject discontinuation

Reasons for discontinuation of GHT will be reported as on a follow-up documentation form (end-of-observation visit, EOO). Reasons include end of GHT, withdrawal of informed consent, change of centre (not participating in INSIGHTS-GHT), lost to follow-up or any other reasons, e.g. administrative.

In case of end of the INSIGHTS-GHT registry, the information, whether the final height is reached and if yes, whether it is the genetic target height, is captured.

In case of lost-to-follow up, efforts should be made to contact the patient (by phone or other channels) in order to collect missing information.

Regardless of the reason, all data available for the subject up to the time of discontinuation should be recorded on the appropriate eCRF. Data collected up to the time of discontinuation will be used in the analysis and included in the clinical registry report.

### Safety reporting

The following safety data must be reported, if any of these events occur in patients treated with a GH product:Serious Adverse Events (SAE)Non-serious Adverse Event (AE)Reports of drug exposure during pregnancyReports of misuse and abuse of productsReports describing the occurrence of other “special circumstances” and “Special scenarios” (irrespective of whether a clinical event has occurred)

AEs are defined as follows: [10]

An untoward medical occurrence after exposure to a medicine, which is not necessarily caused by that medicine. An AE can therefore be any unfavourable and unintended sign (including an abnormal laboratory finding, for example), symptom, or disease temporally associated with the use of a medicinal product, whether or not considered related to the medicinal product.

SAEs are defined as follows: [10]

Any AE or experience that, at any dose,Results in deathIs life-threateningRequires hospitalization or prolongation of existing hospitalizationResults in permanent or serious disability/incapacityIs a congenital anomaly/birth defectIs a medically significant

Medical and scientific judgement should be exercised in deciding whether expedited reporting is appropriate in other situations, such as medically significant events that may not be immediately life-threatening or result in death or hospitalization but may jeopardize the patient or may require intervention to prevent one of the other outcomes listed in the definition above. These should also usually be considered serious.

Definition special scenario:

Includes reports of drug-drug/drug-food interaction, drug use during lactation or breast-feeding, lack of effectiveness, overdose, drug maladministration or accidental exposure, dispensing errors/medication errors, withdrawal or rebound symptoms, irrespective of whether a clinical event has occurred.

“Special Circumstances” mean drug exposure during pregnancy, drug misuse and abuse.

Pregnancies in women receiving GHT must be reported in the same way as AEs. The investigator will follow-up pregnancies to determine outcome (including premature termination) and status of mother and child and report it.

### Reporting channels and timelines

The above-described events and pregnancies will be reported by the electronic data entry form on the website of the INSIGHTS-GHT registry. The investigator will be required to describe the event (type, start and stop dates, severity, seriousness, outcomes etc.). Other relevant information from the current and previous documentations will be automatically added to the report. When the investigator saves the AE form in the database, it will be sent via e-mail to the respective marketing authorization holder (as indicated in the current Summary of Product Characteristics) of the GHT, and in copy to GWT-TUD and the investigator himself/herself (as confirmation).

In case the electronic system should not be accessible, the investigator shall alternatively use paper sheets which should be sent via fax to the respective marketing authorization holder of the GHT.

SAE must be reported within 1 business day after knowledge.

Non-serious AE (e.g., all AE that do not meet the definition of serious) should be reported within 14 calendar days coming to the investigator’s attention.

